### Recruitment {15}

The study site is one of the very few dermato-gynaecology centres in New South Wales and receives a high volume of referrals for patients with vulval disorders, including VLP.

## Assignment of interventions: allocation

### Sequence generation {16a}

The methotrexate and deucravacitinib treatment groups will have a 1:1 ratio of allocation, generated using appropriate statistical software.

### Concealment mechanism {16b}

Treatment allocation will be performed by a separate party, who will feed this data to REDCap. The investigators will not have access to this data on REDCap. Hence, the allocation sequence will be concealed from the investigators and participants. Container labels will use KIT numbers.

### Implementation {16c}

A separate party, who is not involved in other aspects of the study, will generate the allocation sequence and create the randomisation list. The investigators will enrol participants and remain blinded to the treatment allocation.

## Assignment of interventions: blinding

### Who will be blinded {17a}

The investigators, outcome assessors, trial participants and statistician assisting with the data analysis will be blinded.

### Procedure for unblinding if needed {17b}

Unblinding of the treatment allocation will be allowed in events such as medical emergencies, where the safety and well-being of the participant are of concern. The pharmacy will be contacted to assist with unblinding.

## Data collection and management

### Plans for assessment and collection of outcomes {18a}

Study data, including clinical assessments, patient-reported outcomes and other study instruments, will be centralised and entered directly into an electronic data capture (EDC) platform, REDCap. All personnel collecting data will be trained. Investigators will review all data for accuracy and completion.

### Plans to promote participant retention and complete follow-up {18b}

Participants will be provided with emergency contact to assist with prompt management of issues and concerns raised by participants during the trial. If a participant does not attend their scheduled visit, every effort will be made to contact the participant and reschedule their study visit. A follow-up visit will take place 30 days (± 1 week window) after the end of the treatment visit (week 32), or after a premature discontinuation visit.

### Data management {19}

Data will be centralised and entered directly into REDCap, a secure platform supported by the Northern Sydney Local Health District Human Research Ethics Committee.

### Confidentiality {27}

Personal information about potential and enrolled participants will be entered into REDCap, a secure platform supported by the Northern Sydney Local Health District Human Research Ethics Committee.

### Plans for collection, laboratory evaluation and storage of biological specimens for genetic or molecular analysis in this trial/future use {33}

Serum sampling for biomarker evaluation will be collected from all VLP participants at weeks 0, 8 and 32 (or premature discontinuation visit). For tissue sampling, this will be performed on 10 participants with VLP (weeks 0 and 32) and 10 matched healthy controls (once only). Each tissue sampling will involve taking two 3-mm punch biopsies.

The planned investigations include:(i)Serum cytokine mRNA analysis involved in TYK-2-mediated pathway, e.g. IFN-type I (IFN-a), IL-12, IL-23 and IL-17, and downstream pathways including CXCL9/10/11 and IFN-gamma(ii)Tissue cytokine mRNA analysis involved in TYK-2-mediated pathway, e.g. IFN-type I (IFN-a), IL-12, IL-23 and IL-17, and downstream pathways including CXCL9/10/11 and IFN-gamma(iii)Immunohistochemistry with T-cell markers on tissue

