### Sample size {14}

A total of 116 patients will be recruited. The sample size was determined using a *T*-test for independent means (STATA, version 17.0) [38]. We based the calculation of our sample size on a previous RCT comparing the mean change of GELP scores between two intervention groups after 24 weeks of treatment [7]. As the mean reduction in GELP scores in their intervention group of interest was equivalent to a standardised mean difference (SMD) of > 0.80 (large effect size based on Cohen’s* d* measure [39]), we used an SMD of 0.70 (moderate to large effect size) in our calculation. The result of the analysis indicated that a total of 58 participants, or 29 in each deucravacitinib and methotrexate group, will be required to provide 80% statistical power with a two-sided 5% significance level to detect an SMD of 0.70 in the mean change of GELP scores from baseline (week 8) to week 32 between the two intervention arms.

According to the literature, approximately 20–40% of VLP patients would require second-line treatment with systemic immunosuppression to control their disease [9, 13]. In the study by Fahy et al. [9], over 40% of patients required systemic therapy. Based on these, we estimated that half of the participants will be non-responders, and therefore, a total of 116 participants will need to be recruited to provide a sample size of 58 for both the deucravacitinib and methotrexate groups or 29 in each treatment arm.

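### The only assay named for the serum samples is cytokine mRNA, which a cell-free specimen cannot validly supply; the analyte or the blood specimen should be changed

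*Protocol article*

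**What the plan says.** The section of the protocol article on biological specimens {33} sets out the blood sampling: "Serum sampling for biomarker evaluation will be collected from all VLP participants at weeks 0, 8 and 32 (or premature discontinuation visit"). It names no other blood specimen. A list of assays follows, opened by "The planned investigations include". Its first item is "Serum cytokine mRNA analysis involved in TYK-2-mediated pathway", with type I interferon, IL-12, IL-23 and IL-17 as examples, and CXCL9/10/11 and interferon-gamma as downstream markers. The second item is "Tissue cytokine mRNA analysis involved in TYK-2-mediated pathway", with the same analytes. The third is immunohistochemistry on tissue.

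Tissue is taken from 10 participants with the disease, at weeks 0 and 32, and once from 10 matched healthy controls.

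Outcomes {12} lists immunological change and cytokine expression as the last secondary endpoint, in serum at weeks 0, 8 and 32 and in tissue at weeks 0 and 32. It does not say whether expression means protein or mRNA. The same section defines baseline for the primary endpoint as week 8, the visit at which non-responders are randomised.

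**The concern.** Serum is the fluid left once blood has clotted and the cells have been taken away. Cytokine mRNA is made and held in cells. Pairing the two leaves only residual extracellular RNA to measure. That RNA is scarce, partly degraded and influenced by clotting and handling, and it does not track cytokine gene expression in circulating or lesional cells.

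The rationale for deucravacitinib rests on the TYK2 pathway, and the serum series is the plan's main means of observing that pathway in the randomised groups. It comes from all participants and includes a sample at the randomisation visit. Tissue comes from only 10 participants and has no week 8 sample, so its change from week 0 to week 32 also spans the eight-week topical run-in. If the serum assay does not measure what the endpoint asks for, the pathway comparison from the randomisation baseline is lost.

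**Working it through.** The plan gives no figure for this point, so the check sets the sections side by side and then counts the samples concerned.

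**Specimen, assay and endpoint**

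| Element | Where | What is fixed |
|---|---|---|
| Blood specimen | Biological specimens {33} | Serum; no whole-blood, separated-cell or RNA-stabilised sample named |
| Serum assay | Biological specimens {33}, item (i) | Cytokine mRNA; no protein assay and no cell-free RNA method named |
| Tissue assays | Biological specimens {33}, items (ii) and (iii) | Cytokine mRNA and immunohistochemistry |
| Endpoint | Outcomes {12} | Cytokine expression in serum and tissue; analyte not specified |

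1. *Tissue.* Tissue contains cells, so mRNA is a suitable analyte. Specimen, assay and endpoint agree.
2. *Serum, assay as named.* The specimen has no cells and the analyte is a cellular transcript. The assay does not validly give the endpoint.
3. *Serum, endpoint as defined.* The endpoint is wider than the assay. Circulating cytokine and chemokine protein is present in serum and falls within the endpoint's wording, so the specimen can serve the endpoint if the analyte changes.
4. *Likely origin.* Items (i) and (ii) differ in essence only in the words serum and tissue. The mRNA term may have been carried across from one to the other. That is inference; the article does not say so.

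**Samples concerned**

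Inputs: 116 recruited and 58 randomised (Sample size {14}); serum at weeks 0, 8 and 32 (biological specimens {33}).

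- Randomised participants, week 8 and week 32: 58 × 2 = 116 draws. (That this equals the recruitment target is coincidence.)
- Randomised participants, all three time points: 58 × 3 = 174 draws.
- All recruits, all three time points: 116 × 3 = 348 draws.

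The first count fits the point, because it covers the comparison between arms from the randomisation baseline. The last includes the half of recruits expected to respond to topical treatment, who are never randomised. All three are planned numbers before dropout. The 58 is used only to count samples; nothing here depends on the power calculation, which concerns GELP alone.

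**The case against.** The best defence is that the article is a condensation. The trial follows protocol v1.3, which is not shown, and tube type, processing and assay platform usually sit in the full protocol or a laboratory manual. The assay list is open and its cytokines are given as examples, so a protein assay is not excluded. The word serum may be shorthand for a blood sample, or mRNA may be a slip.

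Part of this stands. The absence of a protein assay from the article does not prove that none is planned, and the absence of processing detail is no fault. But the point does not rest on an omission. The article names an assay, and that assay does not suit the specimen it names. An open list does not make a listed item suitable, and if the cause is a slip in wording, the wording still needs correcting.

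A reader might go further and infer that the endpoint cannot be derived from the samples collected, or that all 348 draws would be wasted. The documents do not support either. Outcomes {12} asks for cytokine expression without specifying mRNA, a protein assay on the same serum could supply it, and the tissue part of the endpoint is not in question. Nor can one say that the assay would return mostly undetectable values: the article gives no detection rate, and serum does hold some extracellular RNA.

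**Conclusion.** The concern holds in a limited form. As written, the serum part of the last secondary endpoint is tied to an assay that cannot validly measure it. The same serum could supply the endpoint through protein. About 116 draws from 58 randomised participants, at week 8 and week 32 and before dropout, bear on the comparison that is at risk. That comparison uses the only biomarker specimen taken at both visits.

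The effect is confined to one secondary endpoint of an exploratory kind. The primary GELP analysis and the tissue assays are untouched. The change should be made, but it does not threaten the trial's main result.

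The conclusion rests on two assumptions: that serum carries its ordinary laboratory meaning, and that cellular transcripts are not validly measured in it. The second is general laboratory knowledge, not something the article states. If the full protocol already names a protein assay, or a blood specimen that preserves RNA, only the article's wording needs correcting.

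**What to change.** Choose one analyte for blood and state it in both places.

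- *If protein is intended:* in item (i) under biological specimens {33}, replace serum cytokine mRNA with quantification of serum cytokine and chemokine protein for the same analytes, and name protein as the serum analyte in Outcomes {12}.
- *If transcripts are intended:* keep mRNA, but change the blood specimen at weeks 0, 8 and 32 to one that preserves cellular RNA, and name that specimen in both sections. This has to be settled before samples are processed, since cells removed when serum is prepared cannot be recovered later.

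In either case, keep mRNA for tissue.

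The cost is an amendment to the wording, with the funder and ethics committee approvals the article requires for amendments, and a different assay or tube at draws already scheduled. No visit or procedure is added. The drawback of the protein route is that low-abundance analytes, such as IL-12 and IL-23, may need a high-sensitivity assay.

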## Statistical methods

### Statistical methods for primary and secondary outcomes {20a}

The data will be presented as mean with standard deviation, median with interquartile range, or frequencies with percentages as appropriate. Analysis of covariance (ANCOVA) will be used to compare the mean change in GELP scores from baseline and week 32 between the deucravacitinib and methotrexate groups. Other endpoints will be analysed using independent samples *T*-test, Mann–Whitney *U* test, Fisher’s exact test, ANCOVA model or linear mixed effects model as appropriate. All statistical tests will be performed at a 0.05 level of significance.

### Interim analyses {21b}

N/a—there is no plan for interim analysis.

### Methods for additional analyses (e.g. subgroup analyses) {20b}

We will perform intention-to-treat (ITT) and per-protocol set (PPS) analyses. The number and proportion of screened, randomised, treated and analysed participants will be evaluated.

### Methods in analysis to handle protocol non-adherence and any statistical methods to handle missing data {20c}

The percentage of missing values for all the variables at each time point will be reported. For the primary outcome analysis, the missing values will be imputed using the multiple imputation method. Ten sets of imputed data will be created and analysed using the analysis method described for the primary outcome. The mean difference in mean change from baseline to week 32 between the methotrexate and deucravacitinib groups from the ten imputed analyses will be combined to obtain a pooled common mean difference and 95% CI. A complete case analysis will also be performed to assess the sensitivity of the magnitude and significance of the effects compared. All statistical tests will be performed at a 0.05 level of significance.

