### Criteria for discontinuing or modifying allocated interventions {11b}

A participant may withdraw from the study for any reason at any time.

Permanent discontinuation from the study will take place if a participant:Requires oral corticosteroids for more than four consecutive weeks.Requires rescue treatment with a non-corticosteroid systemic agent (including but not limited to cyclosporine, methotrexate, mycophenolate mofetil, or azathioprine) or injectable or parenteral corticosteroid.Develops clinically significant abnormal laboratory results or adverse events (AEs), which rule out continuation of the study drug, as determined by the investigator.Becomes pregnant or plans to become pregnant during the study.Develops active TB during the study.Develops malignancy, except for localised non-melanoma skin cancers or carcinoma of the cervix in situ.Has a confirmed diagnosis of deep vein thrombosis, pulmonary embolus, or non-cardiac, non-neurologic arterial thrombosis.Takes prohibited medications when the continuation of the study drug would place the subject at risk, as determined by the investigator.Significantly non-compliant with study procedures, which would put the participant at risk for continued participation in the trial as determined by the investigator.

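### Ten imputations give a valid primary analysis but leave avoidable simulation noise; about 100, with a Monte Carlo error check, would remove most of it at no cost

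*Protocol article*

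**What the plan says.** The section on missing data {20c} makes imputation part of the primary analysis, not a side check: "For the primary outcome analysis, the missing values will be imputed using the multiple imputation method". It then sets the number: "Ten sets of imputed data will be created and analysed using the analysis method described for the primary outcome". The differences "from the ten imputed analyses will be combined to obtain a pooled common mean difference and 95% CI". The analysis model, from the statistical methods section {20a}, is ANCOVA: "Analysis of covariance (ANCOVA) will be used to compare the mean change in GELP scores from baseline and week 32". The threshold is fixed: "All statistical tests will be performed at a 0.05 level of significance". The one sensitivity analysis named in {20c} is complete-case: "A complete case analysis will also be performed to assess the sensitivity of the magnitude and significance of the effects compared".

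The sample size section {14} plans 58 randomised women, 29 per arm. No section states an expected proportion of missing week-32 scores.

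**The concern.** Imputed values are random draws. With few imputations, the pooled difference, its standard error and its p-value all depend on the random number seed as well as on the patients. The trial has one primary comparison judged at 0.05. If the p-value falls near that line, the seed could decide on which side it lands.

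Some missing week-32 scores are plausible. The discontinuation section {11b} lists several grounds under "Permanent discontinuation from the study will take place if a participant", and treatment runs for 24 weeks after randomisation. The complete-case analysis has no seed, but it cannot show how far the seed has moved the primary result.

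**Working it through.** **Inputs from the article.** m = 10 imputations {20c}; ANCOVA {20a}; two-sided test at 0.05 {14, 20c}; 58 women, 1:1 {14, 16a}; planning SMD 0.70 {14}. The article gives no derivation for the number ten, so there is no figure to reproduce. The 58 is taken as stated; whether it follows from its own inputs is a separate question and does not affect this point.

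**Assumptions.** 5% to 30% of week-32 GELP scores missing, at random and equally in both arms; baseline correlation 0.5; proper normal-regression imputation from arm and baseline; Rubin's rules with small-sample degrees of freedom; the planning SMD read as 0.70 residual SD.

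**Step 1: noise in the pooled difference.** The Monte Carlo error, in units of the SE, is about sqrt(FMI/m). Simulated FMI was 0.11, 0.22 and 0.31.

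| Missing | FMI | m = 10 | m = 50 | m = 100 |
|---|---|---|---|---|
| 10% | 0.11 | sqrt(0.011) = 0.10 | 0.047 | 0.033 |
| 20% | 0.22 | sqrt(0.022) = 0.15 | 0.066 | 0.047 |
| 30% | 0.31 | sqrt(0.031) = 0.18 | 0.079 | 0.056 |

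Direct simulation agrees. Error at m = 10 was about 0.10, 0.14 to 0.15 and 0.17 to 0.18 SE at 10%, 20% and 30% missing, and 0.07 SE at 5% missing.

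**Step 2: validity and efficiency.** With no true effect, the share of p < 0.05 at m = 10 was 5.4%, 4.1% and 4.3% at 10%, 20% and 30% missing (1,500 trials each; simulation SE about sqrt(0.05 × 0.95/1500) = 0.6 percentage points). Relative efficiency is 1/(1 + FMI/m), which gives 1/1.011 = 0.99, 1/1.022 = 0.98 and 1/1.031 = 0.97. The SE is therefore inflated by at most sqrt(1.031) − 1 = 1.5%.

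**Step 3: how often two seeds disagree on significance.** Each of 1,500 simulated trials with a true effect of 0.70 residual SD was analysed with two seeds.

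| Missing | m = 10 | m = 50 |
|---|---|---|
| 10% | 5.7% | 2.1% |
| 20% | 9.1% | 3.7% |
| 30% | 10.9% | 5.3% |

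The simulation SE is 0.6 to 0.8 percentage points at m = 10 (for example sqrt(0.091 × 0.909/1500) = 0.7). The excess over m = 50 is 3.6, 5.4 and 5.6 points.

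**Step 4: what this means for one borderline result.** Data sets were tuned so that the p-value with 2,000 imputations was 0.03, then re-imputed with new seeds. At 20% missing, the middle 95% of p-values ran as follows:

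- m = 10: 0.013 to 0.077, with 18% of seeds above 0.05
- m = 50: 0.021 to 0.045, with 0.7% above
- m = 100: 0.023 to 0.040, with none above

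At 5% missing and m = 10, only 1% of seeds crossed from p = 0.03, and 13% from p = 0.04.

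**Step 5: is the sample size the cause?** With 580 women, p = 0.03, 20% missing and m = 10, p ran from 0.012 to 0.067, almost the same range as with 58. The driver is FMI/m.

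**Step 6: the m that is needed.** For Monte Carlo error of at most 5% of the SE, m ≥ FMI/0.05²: 0.11/0.0025 = 44, 0.22/0.0025 = 88 and 0.31/0.0025 = 124 at 10%, 20% and 30% missing.

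**The case against.** The strongest defence is that nothing here is wrong. Rubin's rules already carry the 1/m term, type I error holds, and the loss of precision is negligible. All of that stands. A reader might infer that ten imputations bias the result or invalidate the test, and Step 2 shows that they do not.

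Other stronger readings also fail:

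- **That nearly half of seeds would flip the result.** A figure of about 45% does arise at 20% missing, but only in data sets selected to have a large-m p-value of 0.04 to 0.05. Even 200 imputations leave about 14% of seeds above 0.05 in such sets, because any sharp cut-off does this to results lying on it. The unconditional rates in Step 3 are the fair measure.
- **That a trial of 58 is especially exposed.** Step 5 shows otherwise.
- **That much of the primary outcome will be missing.** The article lists grounds for discontinuation but no frequencies. It allows oral corticosteroid rescue of up to four consecutive weeks without withdrawal {11b, 11d}, and it undertakes to contact and reschedule women who miss a visit {18b}.
- **That no seed is fixed.** A seed commonly sits in the statistical analysis plan, which is not shown. A fixed seed would make the run repeatable, although the answer would still depend on which seed was chosen.

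The defence also notes that the week-24 PGA, PtGA and VQLI {12} could serve as auxiliary variables in the imputation. The article does not exclude this. Informative auxiliaries would lower FMI, and the noise would fall with it. This point stands too, so the figures above are for a model without them.

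What survives is narrow: the number ten is fixed in the article, for the primary result, and it leaves noise that more computing would remove.

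**Conclusion.** The point holds as a minor one. Ten imputations are valid but leave noise in the primary difference of roughly 0.10 to 0.18 SE if 10% to 30% of week-32 scores are missing. Under the planning effect, seeds would disagree on significance in about 6% to 11% of trials, against 2% to 5% with 50 imputations. This weakens reproducibility; it is not a bias.

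The size rests on a missing rate that the article does not give, on imputation from arm and baseline only, on a baseline correlation of 0.5, and on reading the SMD of 0.70 on the residual scale. If few scores are missing, or the result is far from 0.05, the choice of ten will not matter.

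**What to change.** In section {20c}, replace ten with about 100 in both sentences that state the number of imputations. Add that the Monte Carlo error of the pooled difference will be reported, and that the number will be raised if this error exceeds about 5% of the SE. On the assumptions above, 100 meets that criterion at 10% and 20% missing (44 and 88 needed), and at 30% it would be raised to about 124. The trigger should be the Monte Carlo error, never the p-value.

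The cost is a few words and seconds of computing, with no effect on patients, data or sample size.

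### Complete case, the named sensitivity check, rests on ignorable missingness just as the imputation does, so neither tests informative dropout

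*Protocol article*

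**What the plan says.** The primary comparison is set out in section {20a} of the protocol article: "Analysis of covariance (ANCOVA) will be used to compare the mean change in GELP scores from baseline and week 32".

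Section {20c} deals with missing scores: "For the primary outcome analysis, the missing values will be imputed using the multiple imputation method". It continues: "Ten sets of imputed data will be created and analysed using the analysis method described for the primary outcome". The ten estimates are pooled. The section then names the check on this analysis: "A complete case analysis will also be performed to assess the sensitivity of the magnitude and significance of the effects compared". It gives no imputation variables and no missingness assumption.

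Section {20b} adds analysis sets: "We will perform intention-to-treat (ITT) and per-protocol set (PPS) analyses". These change who is analysed, not what is assumed about the unseen scores.

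Section {11b} governs leaving the trial: "Permanent discontinuation from the study will take place if a participant" meets one of a list of conditions. Among them are "Requires oral corticosteroids for more than four consecutive weeks" and "Requires rescue treatment with a non-corticosteroid systemic agent", and adverse events or laboratory findings that rule out further study drug. Sections {13} and {18b} provide a premature discontinuation visit and a visit 30 days after it.

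**The concern.** A sensitivity analysis for missing data is useful when it relaxes the assumption on which the primary analysis depends. Here the assumption is that, given the variables used, unseen week-32 GELP scores resemble the observed ones. Complete-case ANCOVA makes that assumption conditional on arm and baseline. Standard multiple imputation makes it conditional on the variables in its model. Neither allows the unseen scores to be systematically worse than those variables predict.

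That possibility is realistic in this trial. A participant who needs systemic rescue or prolonged oral corticosteroids, or who cannot tolerate the drug, leaves the study and may have no week-32 score. The arms are two different drugs, so the rates and reasons may differ between them. If the two planned analyses agree, that agreement could be read as robustness to dropout, which it would not show.

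**Working it through.** **Inputs from the documents.** The primary analysis is ANCOVA of change in GELP from week 8 to week 32 ({20a}, {12}). Missing values are multiply imputed, with complete case as the check ({20c}). Section {14} takes 116 × 0.5 = 58 randomised, or 29 per arm, with no allowance for dropout. The documents give no dropout rate, so there is no missing-data figure to reproduce.

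**Assumptions.** The imputation is of the standard kind, which assumes ignorable missingness, and the ANCOVA adjusts for week-8 GELP. All dropout rates, gains and correlations below are illustrative.

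**1. Size of the possible distortion.** Let completers in the better arm (A) and the other arm (B) improve by g_A and g_B SD. Fractions p_A and p_B drop out, and dropouts gain nothing. Complete case, and imputation from arm and baseline, return about g_A − g_B. The difference over all randomised is (1 − p_A)g_A − (1 − p_B)g_B, so the overstatement is p_A·g_A − p_B·g_B.

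| p_A, p_B | g_A, g_B | Apparent | All randomised | Overstatement |
|---|---|---|---|---|
| 20%, 10% | 1.1, 0.4 | 0.70 | 0.8×1.1 − 0.9×0.4 = 0.52 | 0.18 |
| 20%, 10% | 1.4, 0.7 | 0.70 | 0.8×1.4 − 0.9×0.7 = 0.49 | 0.21 |
| 10%, 20% | 1.1, 0.4 | 0.70 | 0.9×1.1 − 0.8×0.4 = 0.67 | 0.03 |
| 10%, 20% | 1.4, 0.7 | 0.70 | 0.9×1.4 − 0.8×0.7 = 0.70 | 0.00 |

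**2. Do the two planned analyses agree?** A simulation used 29 per arm, SD 1, correlation 0.5 between baseline and week 32, ten imputations, 1,500 runs and a true difference of 0. Poor responders were more likely to be missing in one arm (about 27% missing, against 10% in the other). Bias is in SD units; a negative value favours the arm with outcome-related dropout.

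| Missingness depends on | Imputation uses | Complete case | Imputation |
|---|---|---|---|
| Week-32 score (not at random) | arm, baseline | −0.23 | −0.23 |
| Week-32 score (not at random) | plus a week-24 score | −0.23 | −0.12 |
| Week-24 score | arm, baseline | −0.15 | −0.15 |
| Week-24 score | plus a week-24 score | −0.16 | 0.00 |

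With arm and baseline alone, the two methods agree and share the same bias. With a post-baseline score in the imputation they separate. The imputation is then unbiased if that score explains the dropout, and still biased if it does not.

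**3. What a tipping-point analysis would show.** With 29 per arm, the smallest significant observed difference is t(0.975; 56) × √(2/29) ≈ 0.53 SD. Suppose the observed difference is 0.70 SD and a fraction d of one arm is missing. Holding the standard error fixed, significance is lost when the missing participants are worse than imputed by (0.70 − 0.526)/d:

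- d = 10%: 1.74 SD
- d = 20%: 0.87 SD
- d = 30%: 0.58 SD

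Readers could judge whether such shifts are plausible. The two planned analyses give them no such scale.

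**The case against.** The strongest reply is that this is a condensed article. A full protocol (v1.3) exists, a statistical analysis plan may exist, and either could contain the imputation model and further sensitivity analyses. Section {20c} says complete case will be done as well, not that nothing else will be. That stands as a limit: a reader might infer that no other sensitivity analysis is planned anywhere, and the article cannot show that. The point rests on what {20c} does fix, a named check that does not relax the assumption most in doubt.

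Three other stronger readings also go too far.

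- **That the two analyses will agree whatever the dropout mechanism.** This holds only for imputation from arm and baseline. The imputation model is not given, {12} lists week-24 assessments, and the visit schedule figure is not shown. With post-baseline data the comparison carries some information, as step 2 shows.
- **That treatment failure and toxicity are the main causes of missing scores.** Section {11b} lists its triggers without ranking them, includes pregnancy, tuberculosis, malignancy, thrombosis and non-compliance, and allows withdrawal for any reason. Section {11d} permits oral corticosteroid rescue up to a limit. Prominent routes is as far as the text goes.
- **That an overstatement of about 0.2 SD is to be expected.** That figure puts the higher dropout in the better arm. The reverse gives 0 to 0.03 SD. Assigning dropouts zero gain is also a choice of estimand, not a fact.

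A reader might also fault the use of ten imputations. At 20% missing information the relative efficiency is 1/(1 + 0.2/10) = 0.98, so this is a matter of preference.

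**Conclusion.** The point holds in a limited form. The primary analysis and its named check both rest on ignorable missingness, conditional on different variables, and neither addresses scores missing not at random. The withdrawal rules make that kind of missingness a realistic possibility.

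The size is unknown because the documents give no dropout rate. Under an assumed 20% and 10% dropout without benefit, the overstatement of an apparent 0.70 SD runs from 0 to 0.21 SD, depending mainly on which arm loses more participants. The conclusion assumes standard imputation and applies to the document at hand. It is worth correcting before unblinding, but it does not invalidate the primary analysis.

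**What to change.** Keep multiple imputation as the primary method and complete case as a supplementary analysis. Make these changes to the stated plan:

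1. Add a delta-adjusted tipping-point analysis in which imputed week-32 GELP scores are shifted by amounts varied separately in each arm. Report the combinations at which the conclusion changes.
2. Optionally, add an imputation that centres scores missing after discontinuation for failure or adverse events on the participant's own week-8 GELP.
3. State the imputation model, and include the week-24 PGA, PtGA and VQLI that {12} already lists, together with any data from the discontinuation visit.
4. State that complete case is not a test of informative dropout.

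This needs no new participants, visits or measurements. The cost is wording in the analysis plan, a few hours of programming, and one or two more analyses to report.
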